### Recruitment and implementation

We will recruit participants from the ProA and Kurundata platforms. Study participants will be compensated $1.30 for completing the survey at ProA and 5 RMB at Kurundata. ProA or Kurundata will make the reward payment to study participants. To complete the survey, a potential study participant must open an account on ProA or Kurundata and provide his or her personal information. Participants must agree to ProA’s or Kurundata’s data privacy terms and conditions. ProA or Kurundata will assign each participant a unique, anonymized ID. Because ProA and Kurundata handle the interaction between the study investigators and participants, the participants will be anonymous to the study investigators. ProA and Kurundata are both research platforms with access to large numbers of study participants, enabling us to achieve the desired sample size for this study.

### Assignment of interventions: allocation

All participants who give consent for participation and who fulfill the inclusion criteria will be randomized. After they complete the consent form, Gorilla and Kurundata will use a web-based randomization algorithm to randomly allocate participants to the intervention arm a, intervention arm b, intervention arm c, or control arm (sequence generation) at a 1:1:1:1 ratio. The randomization algorithm involves a web-based algorithm using random permutation, which is independent from the researchers who will recruit patients and implement the protocol. Once an arm of participants is fully recruited, subsequent participants will be randomly assigned to the remaining groups until all arms are fully recruited.

### Assignment of interventions: blinding

The study investigators and those involved in the data analyses and statistics will be blinded to the group allocation.

### Data collection and management

#### Plans for assessment and collection of outcomes

The study investigators will be responsible for data collection. Data will be collected on either the Gorilla or Kurundata platforms. The data retrieved from the platforms will be anonymous. Data downloaded will be stored on an encrypted and secure server. The data will be deleted two years after the study has been completed.

#### Plans to promote participant retention and completion

Participants will be automatically timed out from the online platform if they take more than 45 min to complete the study. Though participants can withdraw the study at any time, they will not be compensated for incomplete survey participation. Incomplete data will be excluded from our analyses. Since the participants are anonymous to us, there is no way to initiate follow-up in the time limit.

#### Data management

Data will be collected on the Gorilla or Kurundata platforms. Third parties except for ProA or Kurundata will not have access to the data. The data will be downloaded and safely stored for statistical analysis on a computing system maintained by the University of Heidelberg in Germany.

#### Confidentiality

Because of the anonymized participant IDs, the study investigators can never meet or know the identity of the study participants. The study investigators will only have access to the participants’ anonymized ID and no other personal or confidential information, and the data will be deleted 2 years after the study has been completed. The study investigators will keep this information confidential.

### Statistical methods

#### Descriptive measures

We will use descriptive statistics to obtain summaries of the demographic data (age, sex, education status, country of residence, etc.).

#### Primary outcomes

For each participant, we will calculate their (COVID-19) vaccine hesitancy score based on their survey responses. Let $$ \overline{K_k} $$ denote the mean vaccine hesitancy for each trial arm, where *k* ∈ {*a*, *b*, *c*} such that *a* represents the intervention arm a (video with storytelling-instructional-humor approach), *b* represents the intervention arm b (video with storytelling-analogy approach), *c* represents the intervention arm c (video with storytelling-emotion-focused approach), and *d* represents the control arm. To evaluate the effectiveness of the video, we will use ANOVA for continuous endpoints and *χ*^2^ test for binary endpoints to assess the statistical significance of the difference between the control arm and the treatment arms. To investigate the factors that affect the endpoints, we will use generalized linear mixed models (GLMM) for the analysis of our endpoints. We use ordinary least squares (OLS) regression for our continuous endpoints; we will use (modified) Poisson regression for our binary endpoints; we will use negative binomial regression for our count endpoints. The reason for the choice of modified Poisson regression for our binary endpoints is that this analysis has good statistical properties and generates risk ratios, which are far easier and safer to interpret than the effect size measures generated by alternative methods (such as odds ratios or marginal effects) [19–22].

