## Objective

Our study aims to achieve the following objectives. To:
Establish the effectiveness of each of the intervention videos in reducing COVID-19 vaccine hesitancy (primary objective).Establish the effectiveness of each of the intervention videos in increasing behavioral intent towards COVID-19 vaccination.Establish the effectiveness of each of the intervention videos in increasing participants’ level of hope.

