### Trial design

Our study is a multi-site, parallel group, randomized controlled trial (RCT) comparing the effectiveness of each of the short intervention videos with each other and with no video (the control condition). Via the online research platforms, participants will be randomly assigned to four intervention arms (Video A: storytelling-instructional-humor approach, Video B: storytelling-analogy approach, Video C: storytelling-emotion-driven approach) and a control arm (no video). Participants will be randomized at a 1:1:1:1 ratio (Fig. 1). In each trial arm, there is a questionnaire survey, arranged in the following order. *Intervention arm a*: participants will receive the storytelling-instructional-humor video, followed by the survey. *Intervention arm b*: participants will receive the storytelling-analogy video, followed by the survey. *Intervention arm c*: participants will receive the storytelling-emotion-focused video, followed by the survey. *Control arm*: participants will first receive the survey. After survey responses are submitted, participants in the control arm will be given access to the video interventions arranged in a single loop (to ensure post-trial access to treatment).

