### Explanation for the choice of comparators

The comparators are similar-length E-E videos, all animated in the same styles by the same animator. They all convey the same message (i.e., vaccines work) using a storytelling approach, without the use of spoken or written language. Each intervention arm video uses a slightly different pedagogical approach. The control arm receives no video intervention. Comparing the *intervention arms a, b* and *c* with the control arm will allow us to quantify the effect of each intervention on the primary and secondary outcomes. Comparing *intervention arms a, b* and *c* with each other will allow us to explore the differential effect of these pedagogical approaches on the primary and secondary outcomes. We will use list experiments, also referred to as the unmatched count technique [15], to eliminate social desirability bias regarding vaccine-seeking behavioral intent. For the list experiments, we will use the control list as the comparator.

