### Outcomes

#### Primary outcome measures

Our primary outcome is vaccine hesitancy (including COVID-19 vaccine hesitancy). We will ask participants how much they agree or disagree with statements related to perceived vaccine safety as well as their attitudes, preferences, beliefs, and hesitancies regarding regular vaccines and the COVID-19 vaccine, respectively [16]. In the statistical analysis process, we will use nine questions to measure the degree of vaccine hesitancy in general and seven questions to measure the COVID-19 vaccine hesitancy specifically. Then we will normalize the final score to a range of 1–5 for both measures for comparison, which higher scores indicate higher degrees of vaccine hesitancy. These questions are shown in Table 1 and the data elicited from this survey will enable us to achieve objective 1.

**Table 1 Tab1:** The (COVID-19) vaccine hesitancy items

Vaccine hesitancy	COVID-19 vaccine hesitancy
L1. Vaccines are important for my health	L1. COVID-19 vaccines are important for my health
L2. Vaccines are effective	L2. COVID-19 vaccines are effective
L3. Having myself vaccinated is important for the health of others in my community	L3. Having myself vaccinated with a COVID­19 vaccine is important for the health of others in my community
L4. All vaccines offered by the government programme in my community are beneficial.	L4. All COVID-19 vaccines offered by the government program in my community are beneficial
L5. New vaccines carry more risks than older vaccines	L5. COVID-19 vaccines from other countries carry more risks than vaccines from my country
L6. I trust the information I receive about shots	L6. The information I receive about COVID-19 vaccines from the vaccine program is reliable and trustworthy
L7. Getting vaccines is a good way to protect myself from disease	L7. Getting COVID-19 vaccines is a good way to protect myself from COVID-19
L8. I am able to openly discuss my concerns about shots with my doctor	L8. Generally, I do what my doctor or health care provider recommends about COVID-19 vaccines for myself
L9. I am concerned about serious adverse effects of vaccines	L9. I am concerned about serious adverse effects of COVID-19 vaccines
L10. People do not need vaccines for diseases that are not common anymore	L10. I do not need COVID-19 vaccines if it’s not a pandemic anymore
L11. I believe that many of the illnesses shots prevent are severe	L11. I am concerned that COVID-19 vaccines might not prevent the disease

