#### Methods for additional analyses (e.g., subgroup analyses)

Since we will conduct the trial in the USA and China, we will conduct both country-specific and cross-country pooled analyses for further comparison.

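### The primary objective is the effect of each video on COVID-19 vaccine hesitancy, but the plan names an ANOVA with no per-video contrast or adjustment and leaves two scores primary

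*Protocol article*

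**What the plan says.** All places are in the protocol article.

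- **Objective.** The primary aim is per video and names one score: "Establish the effectiveness of each of the intervention videos in reducing COVID-19 vaccine hesitancy (primary objective").
- **Trial design.** The trial is described as "comparing the effectiveness of each of the short intervention videos with each other and with no video (the control condition"). With four arms that means three contrasts against control and three between videos.
- **Explanation for the choice of comparators.** Comparing the video arms with control "will allow us to quantify the effect of each intervention on the primary and secondary outcomes". Comparisons between videos are described as exploring differences.
- **Primary outcome measures.** "Our primary outcome is vaccine hesitancy (including COVID-19 vaccine hesitancy"). Two scores follow, nine questions for general hesitancy and seven for COVID-19 hesitancy, each scaled 1 to 5.
- **Statistical methods, Primary outcomes.** "To evaluate the effectiveness of the video, we will use ANOVA for continuous endpoints" (with a chi-squared test for binary endpoints) "to assess the statistical significance of the difference between the control arm and the treatment arms". Regression has a different stated purpose: "To investigate the factors that affect the endpoints, we will use generalized linear mixed models (GLMM) for the analysis of our endpoints".
- **Sample size.** The formula uses the normal quantile at 1 − α/τ, with α = 0.05 and τ = 2 given as the number of comparisons. The text speaks of pairwise comparison between three groups, but the trial has four arms.
- **Methods for additional analyses.** "we will conduct both country-specific and cross-country pooled analyses for further comparison".

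**The concern.** A claim that a particular video reduces hesitancy needs a test of that video against control. A four-arm F test says only that the arm means are not all equal. It can reject because two videos differ from one another while neither differs clearly from control. If it rejects because one video works, it does not identify that video.

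If separate tests against control are meant instead, there are three chances of a false claim, or six if either hesitancy score can carry it, and no adjustment is stated. The objective and the outcome section disagree on whether there are one or two primary scores, and no rule says whether one or both must succeed.

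The sample-size section does count comparisons, so a reader may believe that multiplicity has been covered. The working shows that it has not.

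**Working it through.** **Inputs from the protocol article.** Difference 0.01; SD 0.10 (sensitivity 0.12); α = 0.05; power 80%; τ = 2; equal allocation to four arms; 12,000 per country, so 12,000 / 4 = 3,000 per arm per country. **Assumed:** the correlation between the two hesitancy scores, which the document does not give; the range 0 to 0.9 is shown.

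**1. Reproduce the plan's figure.** n = 2σ² × ((Z(1 − α/τ) + Z(0.80)) / 0.01)², with Z(1 − 0.05/2) = Z(0.975) = 1.960 and Z(0.80) = 0.842.
- SD 0.10: 2 × 0.0100 × (2.802 / 0.01)² = 1,569.8, or 1,570 per arm (6,280 in all), as stated.
- SD 0.12: 2 × 0.0144 × (2.802 / 0.01)² = 2,260.5; the plan states 2,260.

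**2. What τ = 2 does.** The result is the usual size for one two-sided 5% test. Read as two-sided, τ merely splits α between the two tails and corrects for nothing. Read as one-sided, it is a Bonferroni correction for two tests. Neither matches three control contrasts or six pairs.

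**3. Error if the ANOVA is an omnibus F test at 5%, no video effective.**
- One score, one population: 5%.
- Two scores, either may win: 1 − 0.95² = 9.75% at correlation 0; by simulation 8.5% at 0.7 and 7.1% at 0.9.
- If one video works and the F test has rejected, testing the two ineffective videos against control without adjustment gives about 9% error.

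**4. Error if each video is tested against control at an unadjusted 5%, no video effective.** The three contrasts share a control arm, so their pairwise correlation is 0.5.
- One score: P(at least one |z| > 1.96) = 12.5%.
- Two scores, either may win: 1 − (1 − 0.1254)² = 23.5% at correlation 0; by simulation 20% at 0.7 and 17% at 0.9.

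**5. Power after Dunnett adjustment.** The large-sample two-sided 5% critical value for three contrasts against a shared control is 2.349. The expected z at 3,000 per arm is 0.01 / (σ√(2/3000)).

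| SD | Expected z | Power at 1.960 | Power at 2.349 | n per arm for 80% at 2.349 |
|---|---|---|---|---|
| 0.10 | 3.873 | 97.2% | 93.6% | 2,036 |
| 0.12 | 3.227 | 89.8% | 81.0% | 2,932 |

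The last column is the formula of step 1 with 2.349 in place of 1.960. Both values lie below 3,000.

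**The case against.** **The ANOVA may not be an omnibus test.** The sentence goes on to speak of the control arm against the treatment arms, and the sample-size section uses the term ANOVA while sizing pairwise comparisons. Ordinary least squares with arm terms, which the plan also lists, would give per-video estimates. This stands: omnibus is an inference. But if pairwise tests are meant, the 12.5% in step 4 applies, and the regression models are assigned to studying factors, not to testing the videos. The two readings fail in different ways, so the criticisms cannot be added together: the F test does not inflate error for one score, and pairwise tests do address each video.

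**Multiplicity procedures are often left to an SAP.** This also stands, and a missing procedure alone would be weak ground. The point rests on conflicts in the text itself: the objective against the outcome section, the objective against the test, and the comparisons count against the design.

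**Stronger readings that the document does not support.**
- A reader might count the USA, China and pooled results as three further chances of success and arrive at a much higher error rate. The document lists these analyses as additional, for further comparison, and nowhere says that any one of them suffices. What remains is that recruitment is set per country and no population is named as primary.
- A reader might count all six pairs. Contrasts between videos cannot show that a video beats control, and the protocol already calls them exploratory in purpose.
- A reader might treat a win on either score as the stated rule. No rule is given. If both scores had to succeed, the second would add no inflation.

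Whether several treatments sharing one control need familywise adjustment is debated. Here the protocol counts comparisons itself, so it should count them correctly.

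**Conclusion.** The concern holds in a limited form. The stated primary test does not match a per-video objective, the number of primary scores is inconsistent, and the comparisons count is wrong for a four-arm trial.

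The size depends on the reading. As an F test, error is 5% for one score and about 7% to 10% for two, with the effective video left unidentified. As unadjusted contrasts with control, it is about 12.5% for one score and 17% to 23.5% for two. The two-score figures assume that either score may carry the claim and that their correlation lies between 0.9 and 0. The one-score figures need neither assumption.

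**What to change.** 1. Name the COVID-19 hesitancy score as the primary outcome, to match the first objective, and make general hesitancy secondary.
2. State the primary test as three video-versus-control contrasts with Dunnett adjustment (critical |z| about 2.35), reported with adjusted confidence intervals.
3. Correct the sample-size section: four arms, three primary comparisons, and a critical value that matches the test.
4. State which population carries the primary claim.

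This is a change of wording and analysis, to be made before the data are analysed. The power cost is 3.6 points at SD 0.10 (97.2% to 93.6%) and 8.8 points at SD 0.12 (89.8% to 81.0%). No extra recruitment is needed, because 3,000 per arm exceeds the 2,036 and 2,932 required. No further correction across countries is proposed: it is a separate trade-off that could bring power down to about 73% at SD 0.12.

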#### Secondary outcomes

For the vaccination plan in the list experiment, we will calculate the mean score for the control list and treatment list, denoted by $$ \overline{C_i} $$ and $$ \overline{T_i} $$ respectively, where *i* is the index of the list. Then we can calculate the mean difference between the control list and treatment list within each trial arm, which is considered as the participants’ behavioral intent to get vaccinated in this trial arm, denoted as $$ \overline{D_{ik}}=\overline{T_{ik}}-\overline{C_{ik}} $$. Analogous to difference-in-difference analyses, we can identify the effect of each treatment.

For other secondary outcomes, we can use the same statistical procedure described above to assess the effectiveness of our E-E video. We will use R statistical software to undertake the analysis.

#### Interim analyses

No interim analyses are planned.

#### Methods for additional analyses (e.g., subgroup analyses)

Since we will conduct the trial in the USA and China, we will conduct both country-specific and cross-country pooled analyses for further comparison.

#### Methods in analysis to handle protocol non-adherence and any statistical methods to handle missing data

Participants who decide to withdraw from the trial will not be replaced

#### Plans to give access to the full protocol, participant level data, and statistical code

This document is the full protocol. Anyone interested in other data or documentation should contact the corresponding author.

### Oversight and monitoring

#### Composition of the coordinating center and trial steering committee

The trial will be overseen by a trial steering committee (TSC). The TSC will have an independent chairperson and members but also includes the trial collaborators. Two TSC meetings are planned.

#### Adverse event reporting and harms

As this is an online survey, there is very minimal risk for study-related injury or harm. We will present non-threatening video interventions and questions about vaccine attitudes. There are no foreseeable risks to participating in the online study.

#### Ancillary and post-trial care

No ancillary and post-trial care is planned.

#### Dissemination plans

The results of this study will be disseminated through presentations at international conferences and publications in peer-reviewed journals. Results will be used by the study collaborators and their institutions (Stanford School of Medicine, Heidelberg University, Chinese Academy of Medical Sciences, and Peking Union Medical College) to improve the design and universal appeal of future educational and health promotion videos. All investigators who meet authorship criteria will be included as co-authors and anyone who contributed, but does not meet the criteria for authorship, will be acknowledged. No professional author services will be used.

## Discussion

Global government and health authorities have actively engaged in efforts to combat the COVID-19 pandemic, including imposing a variety of strict lockdown policies on regions and countries. Also, since the World Health Organization (WHO) is currently orchestrating the global campaign to fight against the spread of the SARS-CoV-2 virus, the progress of vaccination has dramatically accelerated and it is foreseeable that numerous safe and effective vaccines will come to market by 2022 [23]. However, previous research has indicated that vaccine availability does not guarantee vaccine acceptance, especially given global variations in cultural and educational backgrounds [24]. In this study, we propose using animated, E-E videos to decrease general vaccine hesitancy globally and to evaluate their effectiveness using three innovative approaches.

First, we will use the latest online technology to conduct our multi-site, parallel, randomized controlled trial. ProA, the online platform, enables researchers to connect with individuals around the world who are interested in participating in online studies [25]. Kurundata fills a similar function in China. Second, we will host and deploy our study on the Gorilla platform, which is an experiment builder that provides users with the tools for undertaking online behavioral research. The Gorilla randomization algorithm, which demonstrates the platform’s capability to implement innovative trial designs, will guide us in randomly assigning participants at two levels: (1). Participants will be randomized to the storytelling-instructional-humor video arm, the storytelling-analogy video arm, the storytelling-emotion-focused video arm or no video arm (2). Within each arm, participants will be randomized to control list or treatment list within the list experiment portion of the survey.

Third, we will deploy list experiments to reduce the social desirability bias associated with sensitive questions such as the intention to seek vaccination. Prior research highlights the documented discrepancies between publicly declared vaccine intentions and privately held reservations, including safety and efficacy concerns [24]. Therefore, we have designed the list experiment to minimize social desirability bias toward the behavioral intention questions.

This study is expected to establish the effectiveness of short, animated, E-E videos, using different pedagogical approaches, for improving vaccine confidence. We hope to document a reduction in vaccine hesitancy and guide future E-E video development strategies to support education and health communication campaigns globally.

